#### Therapists

Four clinical psychologists with 3 to 8 years of clinical experience and postgraduate training in psychodynamic psychotherapy receive 2 days of training according to the UPP-depression [18] based on the Supportive-Expressive Time Limited (SETL) manual for MDD proposed by Luborsky [15]. Four clinical psychologists with 4 to 8 years of clinical experience and postgraduate training in CBT receive 2 days of training in pre-structured CBT according to the cognitive behavioral protocol for depression by Bockting and Huibers [19], based on the manual proposed by Beck et al. [20].

Both groups of therapists receive regular supervision sessions (bi-weekly group supervision of 2 hours) by experienced therapists in the respective disciplines.

All therapists are blind to the research hypotheses and the outcome of the screening measures and interviews (see below). In both conditions, therapy length is fixed at 16 to 20 sessions (45 minutes each).

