### Outcomes and study measures

#### Procedure

There are measurement points at intake, before the start of therapy, at every session (limited self-report battery), at every fourth session (extended self-report battery), post-treatment, and at follow-up at 3 and 6 months. In the second wave of the study, additional follow-up is planned at 12 and 24 months, which can be extended if research means are available and if participants consent to prolonged follow-up. All interviews and therapy sessions are recorded on audiotape. Therapists write semi-structured reports of every session including an appreciation of their ability to work along the principles of the respective manuals, a description of the content of the session, and self-report scales. An overview of the full procedure and the respective measures that are used is presented in Table 1 according to SPIRIT guidelines [21, 22].

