### Determination of sample size

Based on the literature, it can be expected that a wrong match between personality style and treatment approach can produce adverse treatment effects [4, 7, 10, 12, 13]. Therefore, we expect a large interaction effect between intervention type and personality size on the primary outcome of size 1.1 (Cohen’s *d*). To detect such an effect at the 5% significance level with at least 80% power, about 26 participants are needed in every intervention group in both strata (i.e., about 104 participants in total).

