### Data analysis

Continuous variables will be summarized with means and standard deviations, median and interquartile ranges, and categorical variables with frequency tables.

The post-treatment score on the HRSD is the primary outcome. The primary hypothesis on the interaction between intervention type and personality style will be tested using a mixed model for the post-treatment score on the HRSD with baseline HRSD score (covariate), type of therapy, personality style, and the interaction of type of therapy and personality style as fixed effects and a random effect for every therapist. The latter is included to account for potential correlation in outcomes of patients assigned to the same therapist. Following the intention-to-treat approach, all randomized patients will be included in the analysis. The proposed mixed model approach is valid under the missing at random (MAR) assumption.

Secondary outcomes based on interviews (SCID and CCI) will be analyzed similarly to the primary outcome. Secondary outcomes based on self-reports (BDI, SCL, OQ, DASS, and idiosyncratic complaints), which are obtained at multiple sessions, will be analyzed using a mixed effects model approach with fixed effects of type of therapy, personality style, and its interaction at every time point; and a random effect for every therapist. The three-way interaction between therapy type, personality style, and time will be assessed to corroborate the primary hypothesis. The estimated evolution over time in each therapy group for each stratum will be graphically displayed. Effect sizes, reliable change indices (RCIs), and clinically significant change will be reported when possible for primary and secondary outcomes.

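### The listed model for the repeated self-report outcomes has no patient-level term, so its supporting three-way test is miscalibrated (secondary outcomes only)

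*Protocol article*

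**What the plan says.** The Data analysis section of the protocol article treats BDI, SCL, OQ, DASS and the idiosyncratic complaints as outcomes "which are obtained at multiple sessions, will be analyzed using a mixed effects model approach". The model has "fixed effects of type of therapy, personality style, and its interaction at every time point; and a random effect for every therapist". No other random term and no residual covariance is mentioned.

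The same therapist effect appears in the primary HRSD model, where its purpose is given: "The latter is included to account for potential correlation in outcomes of patients assigned to the same therapist". That is correlation between patients, not between the scores of one patient.

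The section then gives the repeated-measures model a role in the main argument: "The three-way interaction between therapy type, personality style, and time will be assessed to corroborate the primary hypothesis".

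The Procedure section places assessments "at every session (limited self-report battery), at every fourth session (extended self-report battery), post-treatment, and at follow-up at 3 and 6 months". Table 1 lists BDI-II, SCL-90 and OQ-45 at baseline, sessions 1, 8, 12, 16 and 20, post-treatment, and 3 and 6 months. That makes about 9 values per patient, before the later follow-ups. DASS and the idiosyncratic complaints are rated at every session, so 20 or more values per patient.

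**The concern.** In repeated symptom scores from the same person, the largest correlation is usually within the patient. The article prints a random structure for such data and leaves that level out. An analyst who fits what is printed assumes that, once the therapist is allowed for, a patient's successive scores are independent.

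The resulting errors run in opposite directions. Effects that compare patients and pool over occasions look too precise, because 9 correlated scores count as 9 independent ones. Effects that compare occasions within patients look too imprecise, because the stable part of each patient's score is left in the error term.

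The therapy-by-style-by-time interaction is of the second kind. It is also the test named as support for the primary hypothesis. A null result from it could be an artefact of the model, and its p-value would not have its stated meaning.

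**Working it through.** **Inputs from the article.** 26 patients in each of four cells, 104 in total; 5% level (taken as two-sided); interaction effect 1.1 SD (Determination of sample size). Eight therapists, four per arm; the CBT arm has "Four clinical psychologists with 4 to 8 years of clinical experience and postgraduate training in CBT", and the psychodynamic arm also has four (Therapists). T = 9 occasions (Table 1).

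**Assumptions.** The article gives no within-patient correlation. I take total SD 1 and three patterns: exchangeable correlation ρ = 0.3 to 0.7; first-order autoregressive, AR(1), with 0.8; random intercept plus slope with slope variance 0.3 or 0.6. For power, the therapy-by-style contrast grows linearly from 0 to 1.1 over the 9 occasions. The article states 1.1 for the HRSD; using it for the self-reports is my assumption.

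**1. The plan's own figure.** The article says: "To detect such an effect at the 5% significance level with at least 80% power, about 26 participants are needed". A difference of differences of four cell means has variance 4·SD²/n, so n = 4 × (1.960 + 0.842)² / 1.1² = 4 × 7.85 / 1.21 = 25.95, or 26 per cell. Power at 26 is 0.801. The figure reproduces, and this point does not affect it.

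**2. Time-averaged therapy-by-style effect, exchangeable correlation.** The true variance of a patient's mean is [1 + (T − 1)ρ]/T; the listed model uses 1/T. The ratio of model SE to true SE is 1/√[1 + (T − 1)ρ].
- ρ = 0.3: 1/√3.4 = 0.54
- ρ = 0.5: 1/√5 = 0.45
- ρ = 0.7: 1/√6.6 = 0.39

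Type I error is 2[1 − Φ(1.96 × ratio)] = 0.29, 0.38 and 0.45. The therapist effect does not repair this, because patients of both styles are seen within each therapist.

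**3. Change within patients, exchangeable correlation.** The ratio of model SE to true SE is 1/√(1 − ρ) = 1.20, 1.41 and 1.83 for ρ = 0.3, 0.5 and 0.7. For change from the first to the last occasion it is 1.10 under AR(1) 0.8, and 1.28 and 1.20 under the two random-slope patterns.

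**4. Three-way test.** With time as a factor it has 8 df and critical value 15.51. The noncentrality with the correct exchangeable covariance is (26/4) × 1.1² × Σ(t − 0.5)² / (1 − ρ). With t running from 0 to 1 in eight equal steps, Σ(t − 0.5)² = 60/64 = 0.9375, so this is 7.37/(1 − ρ), or 14.7 at ρ = 0.5. The listed model shrinks the statistic by (1 − ρ), so the effective critical value is 15.51/(1 − ρ), or 31.0 at ρ = 0.5.

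**5. Simulation of the listed model.** 104 patients, 8 therapists, therapist variance 0.05, fitted by REML, 1,000 runs per scenario. In the table, simulated values are in brackets where a closed form also exists. The as-written values in the last three rows are simulated.

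| Pattern | Factor: type I | Factor: power as written | Factor: power, correct covariance | Linear: type I | Linear: power as written | Linear: power, correct covariance |
|---|---|---|---|---|---|---|
| Exchangeable 0.3 | 0.005 | 0.29 | 0.62 | 0.019 | 0.82 | 0.90 |
| Exchangeable 0.5 | 0.0001 (0.000) | 0.17 (0.19) | 0.79 | 0.006 (0.007) | 0.86 (0.88) | 0.97 |
| Exchangeable 0.7 | <0.0001 (0.000) | 0.05 (0.07) | 0.97 | 0.0003 (0.000) | 0.92 (0.92) | 1.00 |
| Random slope 0.3 | 0.000 | 0.24 | 0.63 | 0.034 | 0.87 | 0.91 |
| Random slope 0.6 | 0.000 | 0.21 | 0.46 | 0.050 | 0.78 | 0.79 |
| AR(1) 0.8 | 0.007 | 0.29 | 0.28 | 0.146 | 0.73 | 0.59 |

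Across the simulated scenarios, the time-averaged interaction rejected a true null in 35% to 48% of runs, with model SE 0.38 to 0.45 of the true SE. Together with step 2 this gives the 29% to 48% range.

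**6. Contrast at the last occasion.** Model SE over true SE is 1.00 under exchangeable or AR(1) correlation, and 0.91 and 0.85 under the random-slope patterns.

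**7. Per-session scales.** With 22 occasions and ρ = 0.3 to 0.7, the step 2 ratio falls to 0.37 to 0.25 and type I error rises to 0.47 to 0.62.

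**The case against.** The strongest reply is that the article is silent rather than wrong. It does not say that residuals are independent. Separate effects at each occasion suit a repeated-measures model whose within-patient correlation sits in the residual covariance, and a statistical analysis plan that is not shown may specify it. This stands in part: a reader may not conclude that the trial statisticians intend independence. But the article does more than omit detail. It lists the random structure, and the list carries over the single-occasion model without the level that repetition adds.

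Second, the largest type I errors belong to a time-averaged effect that the article does not name as a test. That is correct. They show what happens to any pooled result from this model. For the named test with time as a factor, the error is conservative, so it would not give false support.

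Third, a reader might infer that the three-way test is close to useless. The figures do not support that in general. Power of 0.05 to 0.19 needs time as a factor and exchangeable correlation of 0.5 or more. With random slopes or ρ = 0.3 it is 0.21 to 0.29. Under AR(1) 0.8 nothing is lost, and a linear-time test keeps 0.73 or more.

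A reader might also infer that therapy-by-style contrasts at each visit are far too precise, or that the article's missing-at-random statement fails for these outcomes. Step 6 contradicts the first. The second misplaces the statement, which closes the paragraph on the primary outcome. Baseline as a covariate, or a single-df post-treatment contrast in place of the three-way test, would be design preferences: Table 1 collects baseline scores, so baseline may be one of the modelled occasions.

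**Conclusion.** The point holds for the secondary self-report outcomes and should be fixed. As written, the model names no source of within-patient correlation for data with about 9 to 20 or more values per patient.

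Taken literally, it gives a three-way test without its nominal level. With time as a factor, type I error is below 1%, and power is 0.05 to 0.29 against 0.46 to 0.97 with the correct covariance under exchangeable or random-slope patterns. With linear time, type I error ranges from about 0% to 15%, depending on the pattern.

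These sizes rest on assumed correlations and on an assumed linear growth of the effect to 1.1 SD. The direction of the errors for pooled effects and for first-to-last change was the same under every pattern tried. The primary HRSD analysis uses one post-treatment value per patient, so neither it nor the sample size is touched.

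**What to change.** Add a patient-level term to the self-report model, beside the therapist random effect:

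- for the scales given every fourth session, an unstructured within-patient residual covariance or another suitable structure (9 × 10 / 2 = 45 parameters with 9 occasions);
- for the per-session scales, a random patient intercept and slope, since an unstructured matrix for 22 occasions would need 22 × 23 / 2 = 253 parameters from 104 patients.

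State that the three-way interaction is tested in that model. If an analysis plan already contains such a term, the article's description should be brought into line with it. The cost is one or two sentences, with no new data and no change to the sample size. The Data management and dissemination plan section already provides for reporting design changes on the Open Science Framework.

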### Ethical principles

The ethical committee of Ghent University Hospital approved the entire study design and informed consent forms. Participants receive extensive written and oral explanation of all research procedures, the implications of their participation, and consent forms for both the research procedures and publishing of results. An elaborate data management plan safeguards the careful handling of confidential data in all stages of the research process.

If a serious adverse event (SAE, e.g., critical suicide risk) manifests, a Data Safety Monitoring Plan (DSMP) will be activated to decide whether or not the patient must be referred for additional interventions (e.g., antidepressant or other medication, residential care). Participants requiring mental health care in any of the follow-up measurements will be referred to adequate care.

### Data management and dissemination plan

The handling of the rich data gathered within this study is carefully planned in line with ethical considerations of privacy and confidentiality. Contact details of participants are kept in an Excel spreadsheet together with the study identifier in a separate locked location and are never used to communicate to any third party other than the researchers who require contact details to contact the participants. Quantitative data are entered into SPSS matrices throughout the study. A postdoctoral researcher conducts a biweekly control of data input. After full completion of data gathering for a participant, an additional check is performed. All data are stored on a secured university server, and back-ups are kept on encrypted USB drives. Therapists use a secured server facilitation to transfer audio files of therapy sessions to the researchers.

The features of the study and any changes to the study design are reported on Open Science Framework [54]. Quantitative data matrices without any identifying information will be made available through OSF as well. All data that imply confidentiality considerations will not be shared publicly, but are saved on the above-mentioned secured university server and can be accessed under specific conditions upon request.

This study results in a wealth of data allowing the investigation of research questions far beyond the primary hypothesis. Consequently, after the primary publication of trial results using primary and secondary outcomes, a number of studies are planned focusing, among other things, on triangulation (comparing different ways of mapping personality style), process clinical predictors (e.g., therapeutic relationship), first-person experiences (e.g., qualitative study of the CCIs), and biomarkers for depression.

## Discussion

Depressive problems are the most widely diagnosed and most widely investigated psychological problems. Numerous outcome studies have indicated the efficacy of psychotherapy and in some cases psychotherapy with medication for depressive disorders [55]. Effect sizes found in these countless randomized controlled trials comparing different interventions or interventions with no treatment are remarkably similar across studies. Moreover, the famous Dodo bird verdict, stating that there is no difference in efficacy between different types of treatment, especially holds in the context of depression [56, 57]. Nevertheless, efficacy remains limited [58], relapse rates remain rather high [59], and, most importantly, there is huge within-group variability observed in outcome research [60, 61]. Despite these important observations, little research aims at disentangling this variability within groups. In this study we want to analyze the effect of an important client variable in depression theory — namely, the personality style — and contribute to the adaptation of therapy to patient characteristics. These patient characteristics are shown to explain a large part of therapy outcomes [62, 63]; thus, the importance of exploring possibly important patient characteristics is beyond doubt. As Cuijpers [55] indicated, “more knowledge on who benefits from which treatment are important goals for future research (p. 292).”

Whether or not the primary hypothesis is confirmed, the unique properties of this study combining multiple methods and perspectives allow further in-depth exploration of processes of change, and both hindering and helpful factors in therapy. Moreover, the richness of the quantitative, qualitative, and biological data administered at multiple time points allows one to extend the primary research on group level with idiographic approaches.

Before designing the current trial, extensive piloting (naturalistic setting, 28 cases followed throughout the whole phase of therapy and follow-up) was done to test and perfect research procedures that are feasible both for participants and therapists. Also, concerning data collection and storage, the pilot study allowed us to construct a detailed manual on all the steps in the whole research process to guarantee that all research assistants can be trained and follow exactly the same procedures.

Recruitment is proceeding as planned, and several strategies (e.g., managing social media, communication with referrers) are implemented to manage recruitment in a timely manner. Recruitment is expected to last one and one-half years.

### Trial status

Recruitment is ongoing.

## Abbreviations

BDI-II: Beck Depression Inventory II
CBT: Cognitive behavioral therapy
CCI: Client Change Interview
CDI: Clinical Diagnostic Interview
DASS: Depression Anxiety Stress Scales
DEQ: Depressive Experiences Questionnaire
ECR: Experiences in Close Relationships questionnaire
HRSD: Hamilton Rating Scale for Depression
IIP-32: Inventory of Interpersonal Problems-32
OQ-45: Outcome Questionnaire 45
OSF: Open Science Framework
PDT: Psychodynamic therapy
PSI: Personal Style Inventory
RCI: Reliable Change Index
SCID-I: Structured Clinical Interview for DSM-IV-TR Axis I Disorders
SCID-II: Structured Clinical Interview for DSM-IV-TR Axis II Disorders
SCL-90: Symptom Checklist -90
SPIRIT: Standard Protocol Items: Recommendations for Interventional Trials
STPP: Short-term psychoanalytic psychotherapy
TRQ: Therapist Relationship Questionnaire
VAS: Visual analogue scale
VTCI: Short Temperament and Character Inventory
ZIL: Self-rating Inventory for Post Traumatic Stress Disorder
